**Methods:**

This is a multicenter, randomized, double-blind, sham-controlled trial. Participants aged ≥ 18 years with mild plaque psoriasis (PASI< 3, BSA < 3%) and overweight (BMI ≥ 24 kg/m^2^) will be randomized (1:1) to receive either verum ACE at 14 specific acupoints or a sham procedure. Interventions will be administered every 2 weeks for 8 weeks. The primary endpoints are the changes in PASI score and BMI from baseline to week 8. Secondary outcomes include the Dermatology Life Quality Index (DLQI), waist circumference (WC), lipid profiles, and systemic inflammatory markers. The safety of the procedure will be monitored through the recording of adverse events and conducting laboratory tests. Participants will be followed through week 32 to evaluate long-term therapeutic durability.

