**Discussion:**

This trial will provide high-quality evidence regarding the “dual-action” potential of ACE in simultaneously improving psoriatic lesions and metabolic dysfunction, establishing its role as an integrative therapy for this specific patient phenotype.

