To bridge this therapeutic gap, Acupoint Catgut Embedding (ACE), emerges as a promising integrative strategy. As a sustained-release form of acupuncture, ACE involves embedding absorbable sutures into specific acupoints to provide continuous stimulation (17–22). By embedding absorbable catgut sutures at specific acupoints, ACE provides continuous and sustained stimulation to elicit therapeutic responses, thereby achieving long-lasting effects (23). Years of research have confirmed its efficacy and safety. In particular, the application of ACE for the treatment of obesity is supported by extensive clinical observations and mechanistic studies (24). Li et al. found that ACE can improve body composition, including reductions in body mass index (BMI) and waist-to-hip ratio (WHR) through appetite regulation, while also ameliorating metabolic parameters such as blood lipid and glucose levels (25–28). More importantly, its mechanism closely with the needs of psoriatic patients: ACE modulates chronic low-grade inflammation by downregulating IL-6, TNF-*α*, and MCP-1, while simultaneously ameliorating leptin resistance and enhancing insulin sensitivity (29, 30).

Despite its therapeutic potential, the clinical adoption of ACE for psoriasis remains hindered by a lack of high-quality evidence. Current research is predominantly limited to small-scale case series or trials with methodological inconsistencies. There is an urgent need for robust, multicenter randomized controlled trials (RCTs) to definitively establish the efficacy and safety of ACE in this specific patient population and to elucidate its underlying biological mechanisms.

This multicenter, double-blind, randomized controlled trial aims to evaluate the efficacy of ACE compared to a sham procedure in patients with mild psoriasis and overweight/obesity. We hypothesize that ACE will demonstrate superior efficacy in reducing both psoriasis severity and metabolic dysfunction, providing a novel integrative strategy for this specific patient phenotype.

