### Research objectives

2.4

*Primary objective*: to evaluate the efficacy of ACE therapy as an adjunctive treatment for improving the PASI score and reducing BMI after 8 weeks in patients with mild psoriasis and overweight.*Secondary objectives*: (1) to assess the changes in secondary efficacy indicators of psoriasis, BMI, waist circumference (WC), WHR and metabolic-related indicators, etc. measures from baseline to week 8. (2) to document the incidence of adverse events (AEs) throughout the study period. (3) to determine the psoriasis recurrence rate during the follow-up period.

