All statistical analyses will be performed using a pre-specified statistical analysis plan. The primary analysis will use a linear mixed-effects model for repeated measures to analyze the changes from baseline in the continuous PASI score and BMI at week 8. As these will be pre-specified co-primary endpoints evaluating distinct therapeutic dimensions, no adjustment for multiple will be applied. Each endpoint will be tested independently at a two-sided significance level of *α* = 0.05. A similar approach will be used for continuous secondary outcomes (e.g., DLQI, WC, lipid profiles, inflammatory markers) will be presented as mean ± standard deviation for continuous variables and as frequencies (n) and percentages (%) for categorical variables. Within-group comparisons (e.g., baseline vs. Week 8) will be analyzed using paired t-tests for normally distributed data or Wilcoxon signed-rank tests for non-normally distributed data. Between-group comparisons will be performed using independent samples t-tests or Mann–Whitney U tests. Categorical outcomes will be compared using Chi-square tests (or Fisher’s exact tests). A two-sided *p*-value < 0.05 will be considered statistically significant. All analyses will follow the intention-to-treat principle. For exploratory outcomes assessed at extended time points (Weeks 12, 16, 24, and 32), the analysis will be primarily descriptive. Data are presented as mean ± standard deviation (or median with interquartile range for non-normally distributed data). No formal between-group hypothesis testing will be performed for these time points, as the data will be intended to illustrate long-term trends rather than confirm treatment efficacy. All statistical tests will be two-sided with a significance level of *α* = 0.05.

Pre-specified subgroup analyses will be performed to explore the heterogeneity of treatment effects on the primary outcomes. Interactions between treatment group and the following baseline covariates will be tested using the linear mixed model by including an interaction term: sex (male, female), age (< 45 years, ≥ 45 years), baseline BMI (< 28 kg/m^2^, ≥ 28 kg/m^2^), baseline disease duration (< 5 years, ≥ 5 years)

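### Testing PASI and BMI each at 0.05 without adjustment is justified by their being distinct dimensions, which is not a valid reason; the plan needs to say whether success requires both

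*Protocol article*

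**What the plan says.** Statistical methods (2.21) gives the reason and the decision in one sentence: "As these will be pre-specified co-primary endpoints evaluating distinct therapeutic dimensions, no adjustment for multiple will be applied". With the sentence that follows, the testing rule reads: "no adjustment for multiple will be applied. Each endpoint will be tested independently at a two-sided significance level" of 0.05. The Methods part of the Abstract names the same pair: "The primary endpoints are the changes in PASI score and BMI from baseline to week 8".

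The aims are worded jointly:

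- The Introduction hypothesises that "ACE will demonstrate superior efficacy in reducing both psoriasis severity and metabolic dysfunction".
- The Abstract's Discussion part speaks of a dual-action potential "in simultaneously improving psoriatic lesions and metabolic dysfunction".
- The primary objective (Research objectives, 2.4) is efficacy for "improving the PASI score and reducing BMI after 8 weeks in patients with mild psoriasis and overweight".

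No section says whether a positive trial requires both endpoints or only one. Sample size calculations (2.11) gives 80% power for one comparison of two proportions, and Limitation (4) says the estimate rests on PASI assumptions and not on BMI parameters.

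**The concern.** Measuring different things does not remove multiplicity. If either of two tests can make the trial positive, there are two chances of a false positive, and the less correlated the tests are, the closer the combined error comes to its independence value. Distinctness is therefore, if anything, an argument for adjusting. What does justify full alpha on each of two endpoints is a rule that both must be significant, because the chance of a false joint claim then cannot exceed the level of a single test. The article does not give that reason.

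Without a stated rule, a significant PASI result with a null BMI result, or the reverse, could be presented as a positive primary result. It would carry more than the nominal error and would not support a claim of benefit on both skin and weight. The choice between the two rules could also be made after the data are seen.

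**Working it through.** **Inputs from the article.** Two primary endpoints, each at two-sided 0.05 (2.21). p1 = 0.60, p2 = 0.25, z-values 1.96 and 0.84, 28 per group, 35 after 20% dropout (2.11).

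**Assumption.** The correlation r between the two test statistics is not given, so a range is shown.

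**1. The plan's own figure.** n = (1.96 + 0.84)² × [0.60 × 0.40 + 0.25 × 0.75] / (0.60 − 0.25)² = 7.84 × 0.4275 / 0.1225 = 27.36, rounded up to 28. Then 28 / 0.80 = 35 per group, 70 in total. Both figures reproduce. The 80% belongs to this one comparison.

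**2. If either endpoint suffices.** With no effect on either endpoint, familywise error = 1 − P(|Z₁| < 1.96 and |Z₂| < 1.96). For independent tests this is 1 − 0.95² = 0.0975. Counting only false findings in favour of ACE, each test has level 0.025, so the value is 1 − 0.975² = 0.0494. For r > 0 the values come from the bivariate normal distribution:

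| Assumed r | Either direction | In favour of ACE only |
|---|---|---|
| 0 | 9.75% | 4.94% |
| 0.3 | 9.51% | 4.76% |
| 0.5 | 9.07% | 4.54% |
| 0.7 | 8.35% | 4.17% |
| 0.9 | 7.04% | 3.52% |

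The comparators are 5% and 2.5% for a single test.

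**3. If both are required.** A false joint claim needs a rejection on at least one endpoint with no true effect, so its probability is at most 5% (at most 2.5% in favour of ACE). No alpha adjustment is needed.

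**4. Power for the joint conclusion (illustration).** Suppose each endpoint had 80% power. Joint power is 0.80² = 64% if independent, 69% at r = 0.5 and 75% at r = 0.9. It can never exceed the smaller of the two individual powers. For 80% joint power with independent endpoints, each needs √0.80 = 89.4%. With the 2.11 formula and PASI rates, that gives 35.97, so 36 per group, and 36 / 0.80 = 45 after dropout.

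**5. If either suffices with alpha split (illustration).** At 0.025 per endpoint, familywise error is 1 − 0.975² = 4.94% for independent tests. The 2.11 formula then gives 33.17, so 34 per group, and 34 / 0.80 = 42.5, so 43 after dropout.

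**The case against.** The strongest reply is that *co-primary* is often used to mean that both endpoints must succeed, and that the jointly worded hypothesis and objective fit this. Testing each endpoint independently can mean simply one test per endpoint, which a both-required rule also uses. On that reading the lack of adjustment is correct and the error is at most 5%. This stands as a possible reading. It does not rescue the stated reason, which appeals to distinctness and not to a joint requirement, and no sentence confirms the rule.

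Three tempting stronger readings are not supported:

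- A reader might infer that the trial, as written, has a false-positive rate near 10% and that a one-endpoint win will be reported as positive. The text is silent on the success rule, so both hold only if either endpoint is allowed to suffice. The 9.75% also assumes independence and counts rejections favouring sham.
- A reader might set that figure against a promised familywise 5%. The article states 5% per endpoint and no familywise level.
- A reader might take 64–69% as this trial's joint power. That assumes 80% on BMI, which the article never gives.

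Other routes to full alpha exist, such as a fixed testing order, but none is stated. Whether two separately reported claims need familywise control is debated, but here the claim is worded as one joint claim. Limitation (4) calls the trial exploratory. Other sections say that it aims to prove a specific benefit, and 2.21 reserves descriptive analysis for the later time points. An unseen analysis plan could hold the success rule, but the article itself fixes the no-adjustment decision and its reason.

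**Conclusion.** The concern holds in a conditional form. The reason given for not adjusting is invalid, and the article does not state the one condition that would make its unadjusted tests valid for its own joint hypothesis. If either endpoint sufficed, familywise error would be 7.0% to 9.75% for correlations from 0.9 to 0, or 3.5% to 4.9% counting only findings for ACE. That is roughly a doubling of the single-test level when the endpoints are weakly correlated. If both are required, error is controlled and what remains is power: the stated 80% is not power for the joint conclusion. The error range rests on assumed correlations, and the joint-power figures rest on a hypothetical 80% for each endpoint.

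**What to change.** Replace the distinct-dimensions justification in Statistical methods with one rule, settled before unblinding and repeated in the analysis plan. The rule that matches the hypothesis and objective is:

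*The trial is positive only if both week-8 PASI and week-8 BMI are significant at two-sided 0.05 in favour of ACE; no alpha adjustment is then needed.*

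If the sponsor means either endpoint to suffice, apply Holm across the two and limit the claim to the endpoint won.

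Also state in Sample size calculations that the 80% refers to one PASI-based comparison and is not power for the joint conclusion.

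**Cost.** One or two sentences and no new data. The both-required rule needs no extra participants only if lower joint power is accepted. In the illustration above, restoring 80% would take 45 per group where 35 are planned. That figure assumes independent endpoints and that BMI is as well powered as PASI, which the article does not establish.

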#### Secondary outcomes

2.19.2

After discussion, the experts reached the following conclusion:

1 Disease severity (assessed at weeks 4 and 8, unless specified)

(1) Improvement rates: PASI (Week 4 only), BSA, and TCM Syndrome score.(2) Calculated as: (baseline score - score at time point) / baseline score.

2 Metabolic and inflammatory parameters (change from baseline; Δ = baseline - week 4/8 value)

These types of parameters include: erythrocyte sedimentation rate (ΔESR), C-reactive protein (ΔCRP), body weight (ΔWeight), waist circumference (ΔWC), waist-to-hip ratio (ΔWHR), body mass index (∆BMI at Week 4 only),lipids and glucose metabolism.

3 Subgroup analyses (change from baseline in participants with abnormal values at baseline)

Additionally, a subgroup analysis was prespecified for patients with abnormal baseline metabolic parameters or metabolic syndrome. For these patients, changes from baseline in HbA1c, fasting serum insulin, uric acid, blood pressure, and lipid levels will be assessed at Weeks 4 and 8. This analysis is in line with methodologies described in previous literature. The changes will be calculated as follows:

Difference of blood pressure (Δsystolic BP) (55): In participants with baseline > 120/90 mmHg (Weeks 4, 8).Difference of fasting plasma glucose (ΔFPG): In participants with baseline > 6.1 mmol/L (Weeks 4, 8).Difference of glycated hemoglobin (ΔHbA1c): In participants with baseline > 6.0% (Weeks 4, 8).Difference of uric acid (∆UA): In participants with baseline > 416 μmol/L (men) or > 358 μmol/L (women) (Weeks 4, 8).

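### Continuous outcomes up to week 8 have two competing between-group analyses, mainly a problem for the secondary outcomes, and the added within-group tests do not estimate the effect of ACE

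*Protocol article*

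**What the plan says.** All of this is in the protocol article, section 2.21 (Statistical methods), unless noted.

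- Primary endpoints, with week 8 as the time point: "The primary analysis will use a linear mixed-effects model for repeated measures to analyze the changes from baseline in the continuous PASI score and BMI". No covariates of the main-effect model are named. The 0.05 level applies to each endpoint separately: "Each endpoint will be tested independently at a two-sided significance level of" that value.
- Continuous secondary outcomes: "A similar approach will be used for continuous secondary outcomes (e.g., DLQI, WC, lipid profiles, inflammatory markers". The sentence then runs on, ungrammatically, into how summaries will be displayed.
- Within arms: "Within-group comparisons (e.g., baseline vs. Week 8) will be analyzed using paired t-tests for normally distributed data", with Wilcoxon signed-rank tests otherwise.
- Between arms: "Between-group comparisons will be performed using independent samples t-tests or Mann–Whitney U tests". No outcome, visit or role (primary, supportive, sensitivity) is attached, and no rule for choosing between the two tests.
- A general threshold of two-sided p < 0.05 follows.
- Categorical outcomes have chi-square or Fisher tests. Weeks 12, 16, 24 and 32 are descriptive, with no formal between-group testing.
- Section 2.19.2 (Secondary outcomes) adds subgroup analyses defined as "change from baseline in participants with abnormal values at baseline".
- Section 2.12 (Intervention) gives both arms urea vitamin E cream, lifestyle and diet education, meal-photo monitoring and step tracking.
- The section also says: "All statistical analyses will be performed using a pre-specified statistical analysis plan". That plan is not shown.

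**The concern.** A mixed model and a two-sample test applied to the same outcome give two p-values. Where no rank is set, the more favourable one can be reported, and the stated 5% error rate no longer describes the procedure. A test on raw change also gives up precision that the baseline value would supply, which counts in a trial of 70.

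The within-arm tests raise a different problem. A significant change from baseline under ACE reflects the shared care, natural variation and regression to the mean as well as any effect of the suture. Printing such p-values side by side invites the inference that ACE worked because one arm reached significance and the other did not.

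**Working it through.** **1. Do the two methods meet on the same outcomes?** Remove what section 2.21 assigns elsewhere: categorical outcomes (chi-square/Fisher) and weeks 12 to 32 (descriptive only). Continuous outcomes at weeks 4 and 8 remain, and the mixed model or its similar approach already covers them. The only separate use left for the t-test/Mann–Whitney sentence is a baseline comparison, which the text does not mention. So the overlap is real.

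**2. The plan's own sample size.** Section 2.11: (1.96 + 0.84)² × [0.60 × 0.40 + 0.25 × 0.75] / 0.35² = 7.84 × 0.4275 / 0.1225 = 27.36, rounded up to 28 per group; 28 / 0.8 = 35; total 70. It reproduces. It rests on a responder proportion, so it says nothing about the continuous analyses. It supplies the 28 per arm used below.

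**3. Reporting the smallest p-value.** The documents give no SD and no correlation r between baseline and week 8, so r is an assumption. Simulated trials with no treatment effect, 28 per arm, complete data, 20,000 per row. ANCOVA of the week-8 value on baseline stands in for a baseline-adjusted mixed model; the other two tests use change from baseline. Each test alone rejects in about 5%.

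| r | Data | Smaller p of t-test and Mann–Whitney | Smallest p of these and ANCOVA |
|---|---|---|---|
| 0.3 | normal | 5.9% | 8.4% |
| 0.3 | skewed | 6.6% | 9.2% |
| 0.5 | normal | 6.0% | 8.1% |
| 0.5 | skewed | 6.4% | 8.6% |
| 0.7 | normal | 5.5% | 7.1% |
| 0.7 | skewed | 6.7% | 8.4% |
| 0.9 | normal | 6.1% | 6.9% |
| 0.9 | skewed | 6.6% | 7.7% |
| 0.97 | normal | 5.8% | 6.4% |
| 0.97 | skewed | 6.5% | 7.4% |

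The last column applies only if the mixed model adjusts for baseline. If it does not, then with complete data its week-8 contrast is essentially the t-test, and the third column applies.

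**4. Precision.** With equal variances at both visits, in units of the outcome variance, raw change has variance 2(1 − r) and the baseline-adjusted outcome 1 − r². The ratio adjusted/unadjusted is (1 − r²) / [2(1 − r)] = (1 + r)/2.

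| r | Ratio | Adjusted power if the change-score t-test has 80% |
|---|---|---|
| 0.5 | 0.75 | 90% |
| 0.7 | 0.85 | 86% |
| 0.9 | 0.95 | 82% |

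At r = 0.97, plausible for BMI over 8 weeks but an assumption, the ratio is 0.985: a gain of 1.5%.

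**5. Within-arm tests.** If the arms do not differ and each within-arm test has power w, exactly one arm is significant with probability 2w(1 − w): 42% at w = 0.3, 50% at w = 0.5, 32% at w = 0.8.

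**6. Abnormal-baseline subgroups.** Participants selected for a high baseline are expected to move towards the mean without any treatment effect. The amount cannot be computed here, because the cut-offs are clinical (for example fasting glucose above 6.1 mmol/L) and no SDs are given. For illustration only, a cut-off 1 SD above the mean gives (1 − r) × 1.525 SD: 0.15 SD at r = 0.9 and 0.46 SD at r = 0.7. Randomisation makes this expected equally in both arms, so the between-arm difference is protected and the within-arm change is not.

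**The case against.** The best counter-argument is that the article already sets a hierarchy where it matters most: "The primary analysis will use a linear mixed-effects model for repeated measures", for PASI and BMI. A t-test on either endpoint is then not the primary analysis. This stands and limits the point. A reader might infer that the primary result itself is open to choice; the label tells against that. The secondary outcomes have no such label.

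Second, a reader might infer that the plan omits baseline adjustment. The article does not say so. It is silent on the covariates of the main model, and an article may leave these to the analysis plan. The loss of precision is certain only for the unadjusted two-sample tests.

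Third, a reader might take the t-tests to be restricted to completers, or the choice between t-test and Mann–Whitney to follow a normality check. Neither is in the between-group sentence. The normality condition is attached to the paired tests, and section 2.21 elsewhere prefers multiple imputation or mixed models. A later line in that section calls for complete cases without imputation, but that conflict is a separate matter.

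Fourth, the plan never offers within-arm significance as evidence of efficacy: its hypothesis is ACE against sham, and subgroup results are called exploratory. That is fair. Misuse is a risk, not a stated intention. The tests still have no inferential purpose in a sham-controlled comparison.

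**Conclusion.** The point holds in a limited form. Section 2.21 gives continuous outcomes up to week 8 two between-group analyses, with no rank between them for the secondary outcomes.

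Selective reporting would raise a nominal 5% to about 6% to 7% when the choice is t-test or Mann–Whitney, and to about 6% to 9% when a baseline-adjusted model is also available. This assumes 28 per arm, complete data and r from 0.3 to 0.97. It is a moderate inflation, and it arises only if the analysis is chosen after seeing the results.

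The upper range and a loss of precision in the mixed model cannot both be claimed: the first requires that the model adjusts for baseline, the second that it does not. For the two-sample tests on raw change, the loss is appreciable at r of 0.5 to 0.7 and negligible for BMI if r is near 0.97.

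The paired tests answer a question the trial does not ask, whatever the value of r.

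**What to change.** In section 2.21:

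1. Name the mixed model as the only inferential between-group analysis of continuous primary and secondary outcomes, and state that the baseline value of the outcome is a covariate.
2. Delete the t-test/Mann–Whitney sentence for efficacy outcomes, or restrict it to a named supportive role with its outcomes and visit given.
3. Report within-group change descriptively, without p-values.
4. For the abnormal-baseline subgroups in section 2.19.2, report the between-arm difference.

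The cost is a change of wording in the protocol and the analysis plan. Baseline PASI, BMI and the other outcomes are already collected at week 0 (Table 1), so no visit, measurement or participant is added. The trial gives up some p-values.

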### Sample size calculations

2.11

Based on our pilot data, the verum ACE achieved an improvement rate of 60%. Since no sham-controlled acupuncture trials for psoriasis are available, we derived the sham group response rate from the placebo effect observed in psoriasis pharmacological trials, which was approximately 25% as reported in the literature (40). Sample size estimation was performed using the standard formula for comparing two independent proportions (two-sided test, *α* = 0.05, power = 80%):

$$n1=n2=\frac{{\left(Z_{1-\alpha /2}+Z_{1-\beta }\right)}^{2}\times [p_{1}(1-p_{1})+p_{2}(1-p_{2})]}{{\left(p_{1}-p_{2}\right)}^{2}}$$

Where p_1_ = 0.60, p_2_ = 0.25, Z_1 − α/2_ = 1.96, and Z_1 − β_ = 0.84. The calculated sample size was 28 participants per group. After adjusting for a 20% dropout rate, the final sample size was determined to be 35 participants per group (total 70 participants).

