Complete blood count, liver function, and renal function: laboratory tests including complete blood count, liver function, and renal function were ordered by physicians and performed by the hospital laboratory.

(1) *ECG*: ECG was ordered by physicians and performed by the hospital ECG department.(2) *AEs*: AEs were reported by study participants during the intervention and follow-up periods, regardless of their relationship to the study intervention.

All data collection time points are shown in Tables 1, 2.

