Analysis of AEs will be performed on the safety population, summarizing the incidence of adverse events and changes in laboratory parameters by treatment group using descriptive statistics. Formula: AEs rate (%) = (number of participants with a treatment-related adverse reaction / total number of participants receiving the treatment) × 100%. The results of subgroup analyses will be interpreted as exploratory.

No adjustment for multiple comparisons will be made for these analyses.

The analysis will handle missing data using a complete-case approach without imputation.

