### Harms

2.22

During the study, local pain, swelling, distension, and itching may occur at the acupoint embedding sites, and adverse changes such as decreased appetite, diarrhea, and constipation may also occur (56–59).

To reduce these injuries, we will strictly screen participants before enrollment. If relevant symptoms already appear, we will systematically assess their severity: (1) If there is local redness and pain, no special treatment is required; keep the area dry, and if the pain is significant, cold compresses can be applied. (2) If local subcutaneous bleeding occurs, apply a cold compress to stop the bleeding, followed by warm compresses to promote bruise absorption. (3) If sutures are expelled, disinfect with iodine solution and avoid pulling them out by yourself; if accompanied by redness and swelling, medical treatment is required. (4) If local induration occurs, it often resolves on its own after surgery; if the induration continues to enlarge, medical treatment is necessary. (5) If allergic reactions or shock should occur, stop the experiment immediately and seek medical treatment as appropriate.

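### The only formula for the adverse event rate counts treatment-related reactions, which does not match the stated objective or the rule for collecting events

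*Protocol article*

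**What the plan says.** Four places in the Protocol article bear on the point.

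- **2.4 Research objectives.** The second secondary objective is "to document the incidence of adverse events (AEs) throughout the study period". It is not limited to events attributed to the procedure.
- **2.17 Plans for assessment and collection of outcome.** On collection: "AEs were reported by study participants during the intervention and follow-up periods, regardless of their relationship to the study intervention".
- **2.21 Statistical methods, opening of the safety paragraph.** "Analysis of AEs will be performed on the safety population, summarizing the incidence of adverse events and changes in laboratory parameters by treatment group", by descriptive statistics. This sentence carries no filter on relatedness.
- **2.21 Statistical methods, next sentence.** "AEs rate (%) = (number of participants with a treatment-related adverse reaction / total number of participants receiving the treatment) × 100". No other formula for adverse events appears in the article.

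**The concern.** The objective, the collection rule and the sentence introducing the safety analysis all refer to adverse events of any cause. The formula that follows is labelled as the adverse event rate but counts only participants whose event was judged to be a reaction to treatment. An analyst who applies it as printed produces an adverse reaction rate and reports it under the name of adverse event incidence.

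The two quantities answer different questions. Comparing events of any cause between randomised arms needs no judgement about causality. A related-only rate depends on that judgement, participant by participant. Safety is in the trial's title, so a reader of the results should be able to tell which quantity is reported. Under the present wording, the label says one thing and the numerator another.

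**Working it through.** **Plan's own figures.** The article states no adverse event count or rate, so there is none to reproduce. The only planned figure used below is the arm size: "the final sample size was determined to be 35 participants per group (total 70 participants" (2.11 Sample size calculations). It reproduces: (1.96 + 0.84)² × (0.60 × 0.40 + 0.25 × 0.75) / (0.60 − 0.25)² = 7.84 × 0.4275 / 0.1225 = 27.36, rounded up to 28; and 28 / (1 − 0.20) = 35.

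**Side-by-side reading.**

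| Place | Quantity | Limited to related events? |
|---|---|---|
| 2.4, secondary objective | Incidence of adverse events over the study | No |
| 2.17, collection | All events reported by participants | No, expressly not |
| 2.21, summary sentence | Incidence of adverse events by group | No |
| 2.21, formula | Rate labelled as that of adverse events | Yes |

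**Direction.** In one arm let N be the participants treated, A those with at least one adverse event of any cause, and R those with at least one event judged related. Everyone in R is also in A, so R ≤ A and R/N ≤ A/N. Equality holds only if every participant with an event has at least one judged related. The shortfall is (A − R)/N, the proportion of treated participants whose events were all judged unrelated. It is a share of participants, not of events: someone with one related and several unrelated events still counts in full.

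**Scale (assumed inputs).** Neither A nor R/A is given. Taking N = 35, A = 7, 14 or 21, and s = R/A from 100% down to 25%, the printed formula returns s × A/35:

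| A of 35 | All-cause incidence A/35 | s = 100% | s = 75% | s = 50% | s = 25% |
|---|---|---|---|---|---|
| 7 | 20.0% | 20.0% | 15.0% | 10.0% | 5.0% |
| 14 | 40.0% | 40.0% | 30.0% | 20.0% | 10.0% |
| 21 | 60.0% | 60.0% | 45.0% | 30.0% | 15.0% |

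For example, 14/35 = 40.0% and 0.50 × 14/35 = 7/35 = 20.0%. Some cells imply fractional participants (0.75 × 14 = 10.5), so the table shows scale only and predicts nothing about this trial.

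**The case against.** The strongest reply is that the sentence just before the formula already commits to an unfiltered summary of adverse event incidence by group. On that reading the formula is an additional rate of related reactions with the wrong name, and nothing is lost. All events are collected in any case, so the all-cause rate can be computed whatever the formula says.

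Much of this stands. The passage supports two readings, and the text does not settle which is meant. But both need a correction: if the formula defines the incidence, the numerator is wrong; if it is an extra rate, the label is wrong. Nor is this detail that an article leaves to a fuller document, because the formula is printed and conflicts with other printed text.

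A reader might infer more than the documents support:

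- *That the published rate will understate harm, or that unrelated events vanish from the comparison of arms.* The summary sentence leaves room for an all-cause table, and even on the related-only reading the two rates can coincide.
- *That systemic events would be filtered out.* Section 2.22 Harms says "adverse changes such as decreased appetite, diarrhea, and constipation may also occur". Events listed there as anticipated harms are not obvious candidates for being judged unrelated.
- *That unblinding would bias the comparison towards safety.* An expelled suture can occur only in the verum arm and could reveal it. Knowing the arm might, however, lead an assessor to attribute more verum events to treatment, which would raise the verum rate. The article does not say who judges relatedness, so no direction can be established.

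**Conclusion.** The inconsistency is real. The rate named for adverse events is defined on treatment-related reactions, against the objective in 2.4, the collection rule in 2.17 and the preceding sentence of 2.21.

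The consequence is conditional. If the formula defines the reported incidence, the figure cannot exceed the all-cause incidence and falls short by the proportion of participants whose events were all judged unrelated. The documents give no means of sizing that proportion. The stronger conclusion, that harm will certainly be understated, is not supported.

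This should be fixed, but it does not threaten the trial. The safety analysis is descriptive, the data needed are collected either way, and the efficacy analyses, alpha and sample size do not depend on the formula.

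**What to change.** In 2.21, replace the single formula with two, by arm and on the same denominator:

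1. **Adverse event rate (%)** = participants with at least one adverse event of any cause / participants who received at least one treatment session (verum or sham) × 100.
2. **Treatment-related adverse reaction rate (%)** = participants with at least one reaction judged related / the same denominator × 100.

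The first answers the objective in 2.4 and uses everything collected under 2.17. The second keeps the present formula under a name that describes it. The change is best made before unblinding, so that the safety numerator is not chosen with the results in view.

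The cost is one redefined formula and one extra table row, with no new data. The published adverse event rate may be higher than the present formula would give.
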